#### Data collection, information sources and follow-up

All variables will be measured individual level. All participants will be invited to attend the PHCC for outcome assessments. The variables will be measured in both groups between 5 and 10 days before the intervention, immediately after the intensive phase (1 month) and after 3, 6 and 12 months of recruitment (Table 2). During the first interview we will measure the height (in meters). The same scale of the PHCC will be used to measure weight. During the follow up phase of the study, the nurse will measure weight and record physical activity for the intervention group. Participants from both groups will receive reminders before follow up visits. For each assessment, one of the study researchers will call up to three times during the day to make the appointment. During the visit, he/she will fill out the questionnaires by interviewing the participant; other clinical data will be extracted from the electronic medical records by the general practitioner or nurse. Empathic communication with study participants will be sustained during all phases. Two independent investigators will enter the data in a centralized database; data quality will be assessed.

#### Randomization

To avoid contamination between study groups, the PHCC will be the randomization unit. The PHCCs that agree to participate will be allocated either to the IG or the CG according to a random sequence generated by a computer programme. The allocation of the PHCC to the study groups will be carried out by an independent researcher. The patients that fulfil the inclusion criteria will be allocated to the treatment group of their PHCC.

#### Blinding

To avoid bias, the informed consent of participants will be obtained before the disclosure of the randomization results. Due to the characteristics of the intervention patients, physicians and nurses will know their group allocation. The analyst will not know the allocation group of the patient.

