#### Inclusion criteria

Level 1. Inclusion criteria to be determined by the physician: primary care patients with clinical and radiological diagnosis of knee osteoarthritis in the Kellgren-Lawrence stages 1–3 [24]; to be able to read and write; to have a mobile phone; to be able to go to the PHCC; and to agree to participate. Level 2. Inclusion criteria to be determined by the psychologist: patients that deliver the “commitment folder” within the period agreed. This report will measure the stage of change [13] of the patient [11].

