**Intervention Programme-follow-up phase**			
**Frequency**	**Goals**	**Contents**	**Components**
Once monthly	Maintain Motivation Weight Control	Positive Reinforcement Empower and Train Laser Questions	1. Motivation Techniques
			2. Group Development Techniques
			3. Evidence-based Information

A psychologist coach is in charge of the intensive phase, which includes motivational, coaching psychology and group development techniques, and evidence based information. Four pillars (mindful presence, authentic communication, self-awareness and safe place) [25] and seven elements that determine behaviour change (self-regulation, skills, self-efficacy, expected outcome, intention, context and regulations) [11] are the cornerstone of health coaching.

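### Consent before disclosure does not by itself prevent selection bias when centres are randomised, and no masking is stated for recruiters or for the WOMAC interviewer

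*Protocol article*

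**What the plan says.** **Allocation.** The primary care centre (PHCC) is randomised, an independent researcher carries out the allocation, and patients inherit the arm: "The patients that fulfil the inclusion criteria will be allocated to the treatment group of their PHCC" (Randomization).

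**Blinding.** The section makes three statements. On enrolment: "To avoid bias, the informed consent of participants will be obtained before the disclosure of the randomization results". On knowledge of the arm: "Due to the characteristics of the intervention patients, physicians and nurses will know their group allocation". On masking: "The analyst will not know the allocation group of the patient". It does not say when physicians and nurses learn the arm, or from whom the result is withheld until consent.

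**Enrolment.** The centre's physician or nurse gives the patient the commitment folder together with the consent form, to be returned within two weeks (Recruitment). The physician decides Level 1 eligibility. Level 2 is headed "Inclusion criteria to be determined by the psychologist"; it consists of handing in the folder on time, and the folder is said to measure stage of change (Inclusion criteria). Elsewhere, "A psychologist coach is in charge of the intensive phase".

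**Measurement.** Baseline falls 5 to 10 days before the intervention. Follow-up is after the intensive phase and at 3, 6 and 12 months. Visits are at the PHCC, where a study researcher sees the patient and "he/she will fill out the questionnaires by interviewing the participant" (Data collection, information sources and follow-up). The main outcome is WOMAC, 24 Likert items with a total of 0 to 96 (Outcomes; Table 2).

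**The concern.** Obtaining consent before disclosure is the standard protection when individuals are randomised: nobody can foresee the next patient's arm. In a centre-randomised trial one disclosure reveals the arm of every later patient in that centre. If the people who approach patients or judge eligibility then know the arm, the intervention centres can enrol a different kind of patient, for example a more motivated one. Randomising centres does not protect against that, and the covariate adjustment planned under Statistical analysis can address only what was measured.

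The second risk is at measurement. WOMAC is a patient's own rating, taken here through an interviewer. Masking the analyst does nothing for what happens in that interview.

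**Working it through.** **1. What the consent rule covers.** Each centre is to recruit 20 patients (Sample size). Two readings fit the text:
- The arm is released once, after the centre's last consent: 0 of 20 patients are enrolled with the arm known.
- The arm is released after each patient's own consent: from the second patient on it is known in the centre, so up to 20 − 1 = 19 of 20 patients could be enrolled with the arm known.

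The plan does not choose between them. Recruitment from consultations, record searches and waiting-room posters suggests that patients come in over time. GPs and nurses are also to be trained for the follow-up phase (Allocation of time), at a time not stated; training during recruitment would reveal the arm.

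**2. Each step against what is stated.**

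| Step | Who | Stated to be unaware of the arm? |
|---|---|---|
| Level 1 eligibility | Physician | No; will know the arm, time not given |
| Folder and consent form | Physician or nurse | No; will know the arm, time not given |
| Consent | Patient | Yes, until consent |
| Level 2 eligibility | Psychologist | Not stated |
| Baseline and follow-up WOMAC | Study researcher, by interview | Not stated |
| Analysis | Analyst | Yes |

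**3. Baseline.** It is tied to the start of the intervention, not to disclosure. Allocation of time also describes a telephone reminder one week (7 days) before a group session. If that applies to the first session, a baseline interview 5 or 6 days before it takes place after the patient has been told of the session.

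**4. Scale (illustration only).** The document gives no figure for the bias. The plan's own sample size comes first:
- SD of change = 14 × √(2 × (1 − 0.6)) = 12.52.
- n per group = 2 × (1.96 + 0.84)² × 12.52² / 5² ≈ 98.5, rounded up to 99; 99 / 0.8 = 123.75, so 124, as stated.
- Design effect = 1 + (10 − 1) × 0.05 = 1.45; 124 × 1.45 = 179.8, so 180, as stated.

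The standard error (SE) of the arm difference uses 180 × 0.8 = 144 evaluable patients per arm:
- Design effect 1.45: 12.52 × √(2 × 1.45 / 144) = 1.78.
- Design effect for 20 × 0.8 = 16 evaluable per centre, 1 + 15 × 0.05 = 1.75: 12.52 × √(2 × 1.75 / 144) = 1.95.

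With no true effect and an assumed between-arm bias b, the two-sided 5% false-positive rate is 1 − Φ(1.96 − b/SE) + Φ(−1.96 − b/SE):

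| Assumed b (WOMAC points) | Share of the 5-point target | SE 1.78 | SE 1.95 |
|---|---|---|---|
| 1 | 20% | 8.7% | 8.1% |
| 2 | 40% | 20.3% | 17.6% |
| 3 | 60% | 39.3% | 33.6% |

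**The case against.** The strongest reply is that the text does not show any of these people to be unmasked at the critical moment.

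- **Recruiters.** A reader might infer that staff who already know the arm do the recruiting. The documents do not support that. The sentence on who will know the arm carries no date and lists patients beside staff, and patients cannot know before consent. It can fairly be read as describing the time after disclosure. Level 1 screening and the folder hand-over would then precede disclosure, and so could the Level 2 check, since the folder goes out with the consent form. The flow chart to which Recruitment refers is not reproduced and may show the order.
- **Psychologist.** A reader might infer that the coach selects the coach's own patients. Both are psychologists, but they are not said to be the same person, and the Level 2 psychologist is not said to know the arm. The criterion is mainly on-time return; stage of change is not stated as a ground for exclusion.
- **Interviewers.** They are nowhere called unmasked, and researchers are not among those listed as knowing the arm. Delivery is by the coach, GP and nurse; assessment is by a study researcher.
- **Omitted detail.** An article may leave operational steps to the full protocol.

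The first three stand, and they limit the point to what is not required or not stated. The last stands only in part. The article does present consent before disclosure as its protection against bias, and with centre allocation that rule is insufficient as written, even on the favourable reading, unless the centre's list is closed first. Interviewing unmasked patients at the randomised centre is likewise a stated procedure for which a better one is available.

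**Conclusion.** The point holds as a cheap improvement. The stated safeguards cover consent and the analyst. They do not require a centre to be fully enrolled before its arm is released, do not place the baseline WOMAC before disclosure, and do not state masking for recruiters, psychologist or interviewer. Selection and detection bias are therefore not excluded; the text does not show that either will occur.

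Their size cannot be estimated from the document. The error rates above rest on an assumed bias, on the plan's SD, correlation, loss and intraclass correlation, and on a design effect of 1.45 or 1.75. They show only that a bias well below the 5-point target would matter. The planned sample size is not affected.

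**What to change.** **Randomization and Blinding.** State that, in each PHCC, the patient list, the Level 2 folder decision, consent and the baseline WOMAC are all complete before the independent researcher releases that centre's allocation to staff, psychologist or patients.

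**Data collection.** State that participants, who must already be able to read and write, complete WOMAC and ICOAP themselves at each visit. The visit is run by an existing study researcher who is not involved in delivery and is not told the arm.

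**Cost.** This mostly reorders existing steps and uses the independent researcher and study researchers already named. Coaching in a centre can start only after its recruitment closes, and the wording on baseline timing and the week-ahead reminder has to be reconciled with the release date. Patients still know their arm and may reveal it at a visit, so self-completion removes the interviewer's influence on the answers but reduces reporting bias only in part.

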#### Sample size

Sample size calculation is based on the minimal significant change in the clinical parameters and in the impact of the osteoarthritis using the WOMAC index [30]. In order to achieve a power of 80% (beta: 0.2) and a significance level (alpha) of 0.05 for a two-tailed comparison, 124 participants will have to be recruited in each group to detect differences equal or higher than 5 units in the Womac index. An estimated standard deviation of 14, a correlation between the first and second measurement of 0.6 and 20% loss to follow-up have been assumed for these calculations. To take into account the randomization by PHCC, we consider a design effect of 1.45 with a mean number of patients per intervention group of 10 and an intraclass correlation coefficient of 0.05 [31]. The required sample size has been estimated at 180 patients per group: 9 primary care teams with 20 patients each will be recruited for each study group. The statistical package GRANMO v7.12 (IMIM, BCN, Spain) was used for sample size calculation.

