### Phase 2: study of effectiveness, cost-effectiveness and cost-utility

#### Design

Cluster randomized clinical trial. The PHCC will be the unit of randomization.

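### The design effect of 1.45 assumes clusters of 10, but each randomised centre recruits 20, so the stated 80% power is about 73% by the plan's own method

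*Protocol article*

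**What the plan says.** The Sample size section of the protocol article says that "124 participants will have to be recruited in each group" "to detect differences equal or higher than 5 units in the Womac index", at 80% power and "a significance level (alpha) of 0.05 for a two-tailed comparison". The assumptions are "An estimated standard deviation of 14", a correlation of 0.6 between the first and second measurement, and 20% loss to follow-up.

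To allow for randomisation by centre, the section then applies "a design effect of 1.45 with a mean number of patients per intervention group of 10" and an intraclass correlation coefficient (ICC) of 0.05. This gives 180 per group, and the section states how they will be recruited: "9 primary care teams with 20 patients each will be recruited for each study group".

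The level of clustering is stated consistently elsewhere. Under Design, "The PHCC will be the unit of randomization". Study setting gives 18 centres, 9 per group. Randomization repeats that the centre is the unit, and Statistical analysis makes the centre the random effect.

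**The concern.** The usual design effect is 1 + (m − 1) × ICC, where m is the number of analysed patients in the unit that is randomised. The plan uses m = 10, while its next sentence puts 20 patients in each randomised centre. No section makes a group of 10 the randomised or the modelled unit. The inflation for clustering is therefore too small at the stated ICC, and 180 per group does not give the stated 80% power for the primary outcome. The chance of missing a true 5-point difference is larger than the plan tells its readers.

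**Working it through.** **Inputs** (Sample size and Study setting): difference 5; SD 14; correlation r = 0.6; two-sided alpha 0.05; power 80%; loss 20%; ICC 0.05; 9 centres of 20 per group.

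**1. Reproduce the plan's figures**
- SD of the change score: 14 × √(2 × (1 − 0.6)) = 12.52.
- Evaluable per group: 2 × (1.960 + 0.842)² × 12.52² / 5² = 98.5, rounded up to 99.
- Allowing for 20% loss: 99 / 0.8 = 123.75, rounded up to 124.
- Design effect with m = 10: 1 + 9 × 0.05 = 1.45.
- 124 × 1.45 = 179.8, rounded up to 180.

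Power check: 180 × 0.8 = 144 evaluable per group. Effective size is 144 / 1.45 = 99.3. SE = 12.52 × √(2 / 99.3) = 1.777. Power = Φ(5 / 1.777 − 1.960) = 80.3%.

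The chain reproduces exactly, so the cluster size can be examined on its own.

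**2. Replace only the cluster size**
- Evaluable per centre: 20 × 0.8 = 16, and 9 × 16 = 144 per group, as above.
- Design effect: 1 + 15 × 0.05 = 1.75.
- Effective size: 144 / 1.75 = 82.3. SE = 12.52 × √(2 / 82.3) = 1.952.
- Power: Φ(5 / 1.952 − 1.960) = 72.6%.
- Difference detectable with 80% power: 2.802 × 1.952 = 5.5 points.
- Size that the plan's own method would need: 99 × 1.75 / 0.8 = 216.6, so 217 per group.

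**3. Degrees of freedom, a separate matter**

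Eighteen centres in two arms leave 16 degrees of freedom for a between-centre comparison. Power from the noncentral t distribution:

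| Design effect (144 evaluable per group) | Normal | t, 16 df |
|---|---|---|
| 1.45 (as planned) | 80.3% | 75.2% |
| 1.75 (16 per centre) | 72.6% | 67.2% |

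Read across, the 16 df cost about 5 points. Read down, the cluster-size error costs about 8 points on either scale. With 1.75 and 16 df the detectable difference is about 5.8 points.

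**4. What ICC would justify 1.45?**

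0.45 / 15 = 0.030 with 16 evaluable per centre, or 0.45 / 19 = 0.024 with 20. The plan states 0.05.

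**5. Baseline adjustment**

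If the analysis adjusts for baseline, the residual SD is 14 × √(1 − 0.6²) = 11.2. At a design effect of 1.75, SE = 11.2 × √(2 / 82.3) = 1.746 and power is 81.7% (76.7% with 16 df).

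**The case against.** **Ten may be the size of a coaching group.** The plan's phrase can be read that way, and the choice of morning or afternoon sessions would fit two groups per centre. The article does not say so, and it would not help. Patients in two coaching groups at one centre are randomised together and share that centre's clustering. Control centres give usual care and have no coaching groups. The paragraph itself ties the adjustment to randomisation by centre.

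**The planned analysis may be more efficient than the sizing calculation.** This stands in part. Statistical analysis specifies mixed models over all time points, adjusted for confounders and clinical variables, and baseline adjustment could bring power back to about 82%. But the figure of 124 follows from change-score variance, the same section describes the effect as change minus change, and the article does not fix how baseline enters the model. The 73% therefore corrects the plan's sizing statement. It is not shown to be the power of the final model.

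**The loss of power can be made to look larger than it is.** A reader might infer that true power is as low as 62% to 68%. Those figures come from applying the design effect for 20 per centre, 1 + 19 × 0.05 = 1.95, to 144 evaluable patients (68.0% normal, 62.5% with 16 df). That counts the 20% loss in the sample size but ignores it in the cluster size. If all 20 per centre were analysed, there would be 180 per group, and 1.95 would give 77% (72% with 16 df). Inflating 124 by 1.95, to 242 per group, is a defensible conservative planning bound, but it does not describe the power of this design. Nor may the 16-df loss be charged to the cluster-size error, because it also applies to the plan's own 1.45.

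**Nothing here biases the result.** Correct. The centre is a random effect, so this point does not affect the validity of the estimate or the type I error, and the confidence interval will show the precision actually reached.

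**Conclusion.** The sample-size statement is wrong as written. The design effect uses 10 patients per cluster where the randomised and modelled unit recruits 20. On consistent inputs, power for 5 WOMAC points is about 73% by the plan's normal method, not 80%, and the difference detectable with 80% power is about 5.5 points. With 16 degrees of freedom the figures are about 67% and 5.8 points, of which the cluster-size error accounts for about 8 percentage points of power.

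The result rests on these assumptions:
- The plan's SD, correlation, ICC and loss are taken as given.
- Losses are spread evenly, with 16 evaluable in every centre.
- The comparison is of change scores at one follow-up time. The figure of 124 would also follow from SD 14 with neither the correlation nor the loss used, because the factors 2 × (1 − 0.6) and 1 / 0.8 cancel against the plain two-sample formula. The change-score reading is used here because it takes up every input that the plan states.

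The documents do not support a figure near 62%, nor a conclusion that the trial must recruit more patients.

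**What to change.** In the Sample size section, replace the cluster size of 10 with the number per centre (20 recruited, about 16 evaluable) and the design effect of 1.45 with 1.75. Keep 360 patients in 18 centres. Restate the power in one of these forms, naming the method:
- about 73% for a 5-point difference (67% with 16 degrees of freedom); or
- 80% for a difference of about 5.5 points (5.8 with 16 degrees of freedom).

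If a baseline-adjusted primary analysis is adopted and stated, the figure may be based on it: about 82% for 5 points (77% with 16 degrees of freedom) at a design effect of 1.75. This assumes that the correlation is 0.6 and that the ICC of 0.05 also holds after adjustment.

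If 10 was meant as the size of a coaching group, say so, and keep it out of the adjustment for randomisation by centre.

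The cost is a reworded paragraph and a less favourable power statement. No extra patients or centres are needed.

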#### Statistical analysis

Data will be analyzed on an intention-to-treat basis following CONSORT CLUSTER criteria to avoid bias by incomplete datasets. Missing values will be replaced by multiple imputation methods. The non-response bias will be monitored and evaluated during follow up. According to the distribution of the variables, descriptive analysis will be carried out using the mean (standard deviation), median (interquartile range) or frequency (percentage).

For comparisons within and between the intervention and control groups we will use Student t-tests for independent and paired data, McNemar, Chi-Square, Fisher’s Exact test, analysis of variance and the corresponding non-parametric tests when appropriate.

To evaluate the effectiveness of the intervention between both groups during follow up, the change in the intervention group minus the change in the control group, as well as the standardized effect size (SES) will be calculated. SES will be calculated as the mean difference between both groups divided by the standard deviation of the control group. To detect differences within each group, the difference between the means at baseline and at each follow up time and the effect size or standardized response mean (SRM) following Kazis’method will be calculated [32]. The SRM will be calculated as the mean change divided by the standard deviation of the change. To evaluate SRM and SES we will use Cohen’s rule, which classifies effect size as small (0.2-0.5), medium (0.5-0.8) and large (>0.8).

We examined the effects of intervention over all time points using mixed-effects models on repeated measures.

Multilevel ordered logistic regression will be used for the response variable “physical activity”, in which patients are categorized in three levels: low: <600 METs. min/week; moderate: > = 600 and <1500 METs min/week; high: between 1500 and 3000 METs min/week.

The PHCC will be considered a random effect. The intraclass correlation coefficient will be calculated to determine which percentage of variability in the response is due to the PHCCs. The final models will be adjusted for potential confounders and relevant clinical variables. Interactions and colinearity will be evaluated [33]. Significance level of the model has been set at 5%. The statistical packages SPSS for Windows, v.21 (IBM SPSS Inc., Chicago, IL) and Stata/SE v.12 for Windows (StataCorp. LP, TX) will be used for statistical analysis.

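### Patient-level tests are prescribed for between-arm comparisons in a centre-randomised trial, beside multilevel models, without saying which analysis decides the WOMAC conclusion

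*Protocol article*

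**What the plan says.** All references are to Phase 2 of the protocol article.

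- **Design:** "The PHCC will be the unit of randomization". The Randomization section repeats it and gives the reason: "To avoid contamination between study groups, the PHCC will be the randomization unit". Study setting gives 18 centres, nine per arm.
- **Sample size:** clustering is acknowledged and given a value: "we consider a design effect of 1.45 with a mean number of patients per intervention group of 10 and an intraclass correlation coefficient of 0.05". The recruitment plan is "9 primary care teams with 20 patients each will be recruited for each study group".
- **Statistical analysis, simple tests:** "For comparisons within and between the intervention and control groups we will use Student t-tests for independent and paired data". The sentence goes on to McNemar, chi-square, Fisher's exact test, analysis of variance and non-parametric counterparts. It names no outcome or time point, mentions no adjustment for centre, and is not confined to baseline or descriptive use. Descriptive summaries have already been covered in the paragraph before it.
- **Statistical analysis, effectiveness:** the next paragraph defines the effect as the difference between arms in change, with a standardised effect size, and names no model.
- **Statistical analysis, models:** mixed-effects repeated-measures models follow for the intervention effect over time, then multilevel ordered logistic regression for physical activity. The section then says: "The PHCC will be considered a random effect". It plans to estimate the intraclass correlation and sets a 5% significance level for the model.

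The Abstract lists the multilevel repeated-measures analysis under data analyses. The limitations paragraph of the Discussion relies on the multilevel analysis to account for variation in practice.

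**The concern.** An independent-samples t-test, or a chi-square test between arms, takes its standard error from the number of patients. Here the randomised units are 18 centres, and patients of one centre are expected to resemble each other. The protocol accepts this when it inflates the sample, then names between-arm tests that assume an intraclass correlation of zero.

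Two things are at stake. First, a between-arm p-value from a simple test would be too small and its interval too narrow. Second, the same WOMAC contrast could carry two p-values, one from a t-test on change and one from the multilevel model, and the text does not say which one counts. The simple test is the more likely of the two to cross 5% by chance.

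**Working it through.** **1. Inputs, all from the Sample size section**

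- Error rate and group size: "a significance level (alpha) of 0.05 for a two-tailed comparison, 124 participants will have to be recruited in each group to detect differences". The difference sought is 5 WOMAC units, with 80% power.
- Variability and loss: "An estimated standard deviation of 14, a correlation between the first and second measurement of 0.6 and 20% loss to follow-up".
- Clustering: intraclass correlation 0.05, design effect 1.45 at a cluster size of 10.
- Recruitment: 9 centres × 20 patients = 180 per arm. After 20% loss, 20 × 0.8 = 16 per centre.

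**2. The protocol's own figures reproduce**

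- SD of change = 14 × √(2 × (1 − 0.6)) = 12.52.
- n per arm = 2 × [12.52 × (1.960 + 0.842) / 5]² = 98.5, rounded up to 99.
- With 20% loss: 99 / 0.8 = 123.75, rounded up to 124.
- Design effect = 1 + (10 − 1) × 0.05 = 1.45; 124 × 1.45 = 179.8, rounded up to 180.

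So the stated 124 and 180 are recovered, and the 0.05 is the value the plan actually used.

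**3. Error rate of a between-arm test that ignores centre**

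With m patients per centre and intraclass correlation ρ, the true variance of the difference in means is DE = 1 + (m − 1)ρ times what the patient-level test assumes. The standard error is therefore too small by a factor √DE, and a nominal two-sided 5% test rejects a true null with probability about 2 × [1 − Φ(1.96 / √DE)].

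At ρ = 0.05:

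- m = 16: DE = 1 + 15 × 0.05 = 1.75; √DE = 1.32; 1.96 / 1.32 = 1.48; rate 13.8%.
- m = 20: DE = 1 + 19 × 0.05 = 1.95; √DE = 1.40; 1.96 / 1.40 = 1.40; rate 16.0%.
- m = 10, the cluster size in the protocol's own design effect: DE = 1.45; rate 10.4%. The recruitment plan is 20 per centre, so 16-20 is the relevant range.

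**4. Sensitivity to the intraclass correlation, which is an assumption**

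| ρ | 16 per centre | 20 per centre |
|---|---|---|
| 0.01 | 6.8% | 7.2% |
| 0.02 | 8.6% | 9.5% |
| 0.03 | 10.4% | 11.8% |
| 0.05 | 13.8% | 16.0% |
| 0.10 | 21.5% | 25.0% |

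Every entry exceeds 5%.

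**5. Check by simulation**

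20,000 null trials were simulated for each cluster size, with 9 centres per arm, normal outcomes and ρ = 0.05. The patient-level t-test rejected in 13.5% (16 per centre) and 16.5% (20 per centre). A t-test on the 9 v 9 centre means rejected in 5.0% of trials in both cases. The excess comes from ignoring centre, and an analysis that respects centre removes it.

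**The case against.** The strongest reply is that the effectiveness analysis already handles clustering. The section plans mixed and multilevel models with the centre as a random effect, estimates the intraclass correlation and follows the CONSORT guidance for cluster trials. The Abstract points to the multilevel analysis and mentions no t-test. Apart from the planning alpha in the Sample size section, the only stated significance level is the model's. The sentence on simple tests reads like a generic list placed after the descriptive statistics, so it may mean only preliminary bivariate comparisons.

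Much of this stands. A reader might infer that the trial as a whole runs a 14-16% false-positive risk. The document does not support that: the rate belongs to the listed between-arm tests and arises only if they are used for inference. It does not apply to the multilevel models. Nor does it apply to the paired and McNemar tests, which compare within a group. The size is also conditional. The intraclass correlation is a planning value, and the protocol does not say whether it refers to raw scores or to change.

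The reply does not remove the defect. The sentence prescribes these tests for comparisons between the arms, with no restriction to description, and no sentence makes the model decisive. A later analysis plan could settle the order, but the protocol has already named tests that do not fit its design.

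Two further inferences go too far. One is that the models rely on a normal reference distribution with only 18 centres. The text specifies no reference distribution, and degrees-of-freedom methods are commonly left to the analysis plan. The other is that costs will be compared with unadjusted tests. The economic section names no such test; it is only silent on clustering.

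**Conclusion.** The rule is wrong as written, in a limited sense. It gives invalid between-arm p-values if followed, and it sits beside a valid analysis of the same contrast with no stated precedence. At the protocol's assumed intraclass correlation of 0.05 and 16-20 patients per centre, the simple tests would have a true error rate of about 14-16% instead of 5%, with standard errors too small by a factor of 1.32-1.40. The figures assume equal cluster sizes and use a large-sample approximation, which the simulation bears out. A smaller or larger correlation moves the rate between about 7% and 25% over the range examined. Because the appropriate model is already planned, this is a point that should be fixed, not evidence that the trial's main analysis is invalid.

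**What to change.** In the Statistical analysis section:

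1. Remove the independent t-test, chi-square, Fisher, analysis of variance and non-parametric tests from between-arm inference. Keep descriptive summaries by arm, or replace the tests with cluster-adjusted versions.
2. State that every between-arm estimate, interval and p-value for the primary and secondary outcomes comes from the model with a centre random effect, and that this model decides the WOMAC conclusion.
3. In the economic evaluation section, state that the comparison of costs between arms also allows for clustering by centre.

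As optional advice, a small-sample degrees-of-freedom correction suits a model with 18 centres (18 − 2 = 16 degrees of freedom for a comparison of centre means). Its absence is not an error in this document.

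The cost is a few sentences and no new data or design change. Intervals will be wider for any comparison that would otherwise have used the simple tests, which reflects the real uncertainty.
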